#### Assessment of outcomes and blinding

A distant internet randomisation service is used to allocate women to the trial groups. The research team informs women of their allocation after completion of the baseline assessment at the home visit. The randomisation is stratified by baseline EPDS score (13–16 or ≥16). At baseline we collect demographic data; this includes age, marital status, ethnicity, social class, parity, method(s) of infant feeding, history of psychiatric illness, referral(s) to psychiatric and/or mental health services, mode of delivery, level of social support, current medication and pregnancy and antenatal exercise patterns as well as all the outcome measures.

Outcome measures will be assessed at baseline, six months (immediately post intervention) (primary) and 12 months post randomisation. At baseline, the questionnaires (see exception below) are completed and weight is assessed at the home visit. Those randomised to wear the actiheart have the device fitted at the home visit and are asked to wear it for three consecutive days. The research team collect the actiheart from participants and the IPAQ is then completed.

At follow ups, the questionnaires are mailed to all participants at the appropriate time and collected by home visits from the research team. Weight is also measured at the follow up home visits. Those wearing the actiheart have the device fitted at the home visits, are asked to wear it for 3 consecutive days and then complete the IPAQ.

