### Inclusion and exclusion criteria

#### Inclusion criteria

· An ICD-10 diagnosis of depression, following screening using the EPDS at 10–14 and 12–16 weeks and CIS-R at 13–17 weeks after giving birth. Women with a mixed diagnosis of anxiety and depression are also eligible

· Aged 18 years or more

· Currently inactive (defined as not meeting the current public health guidelines for physical activity (i.e. <150 minutes of moderate intensity physical activity per week in previous 7 days))

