##### Case definition (home visit at 12–16 weeks after birth)

In order to rule out the possibility of transient depression, women who score >10 on the first EPDS at 10–14 weeks complete a second EPDS about two weeks later at 12–16 weeks by telephone. Women who score >12 on the second EPDS at 12–16 weeks complete a Clinical Interview Schedule-Revised [26] (CIS-R) at a home visit. Based on the information obtained in the CIS-R, women are assessed as being a case according to the ICD-10 depression criteria. Women with a mixed diagnosis of anxiety and depression are also considered a case.

The trial participant information sheet is sent to women at least 2 days prior to the CIS-R home visit and women have already received an information letter from their GP. Women are given the opportunity to ask questions during the home visit before providing written informed consent for the trial. Eligible women complete the baseline questionnaires at the home visit, prior to randomisation.

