### Analysis plan

Baseline characteristics of participants will be tabulated by randomisation arm. Primary analysis will compare mean EPDS score at the 6 months follow-up between trial groups, adjusting for baseline scores using analysis of covariance. Similar analyses will be conducted for the secondary outcomes. Secondary analyses will adjust for covariates (e.g. age, gender, initial weight, ethnicity, education level) again using analysis of covariance. To explore any longer term effects, a repeated measures mixed model analysis of the primary and secondary outcomes will be undertaken, comparing groups across the 6 and 12 month time points. EPDS score taken at the home visit will be used as the baseline score in analyses. We will also report data on the proportion of women in each group who score less than 13 points on the EPDS at follow-up. All analysis will be by intention to treat.

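### As most naturally read, baseline physical activity is completed after women learn their allocation, yet the ANCOVA would adjust the activity outcomes for it

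*Protocol article*

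**What the plan says.** All places are in the protocol article.

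- Case definition: "Eligible women complete the baseline questionnaires at the home visit, prior to randomisation".
- Assessment of outcomes and blinding, on disclosure: "The research team informs women of their allocation after completion of the baseline assessment at the home visit".
- Same section, on what is done at the visit: "At baseline, the questionnaires (see exception below) are completed and weight is assessed at the home visit". The exception emerges from what follows. Women assigned to the Actiheart "have the device fitted at the home visit and are asked to wear it for three consecutive days", and afterwards "The research team collect the actiheart from participants and the IPAQ is then completed".
- Same section, on what is collected at baseline: demographic data "as well as all the outcome measures".
- Secondary outcomes: physical activity is measured by accelerometer in a random half of the women and by IPAQ-short.
- Analysis plan: the primary analysis is an analysis of covariance on EPDS adjusted for its baseline, and "Similar analyses will be conducted for the secondary outcomes". The EPDS baseline is fixed as the home-visit score. No corresponding statement is made for physical activity.

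**The concern.** A baseline covariate is safe in a randomised comparison because allocation cannot have affected it. The accelerometer record, and the IPAQ in device wearers, come into existence only in the days after the home visit. If allocation has been disclosed at that visit, these values are measurements under known allocation. Women cannot be blinded to an exercise programme, and knowing the arm may change what they do or what they report.

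An arm difference already present in the so-called baseline is then partly subtracted from the six-month activity effect. Physical activity heads the list of secondary comparisons in Aims and Objectives. It also helps to interpret the EPDS result: if EPDS does not differ, the activity contrast indicates whether exercise failed to help or women did not exercise more.

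**Working it through.** **Order of events**

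| Step | When | Source |
|---|---|---|
| Questionnaires other than the exception; weight | Home visit, questionnaires before randomisation | Case definition; Assessment of outcomes and blinding |
| Actiheart fitted | Home visit | Assessment of outcomes and blinding |
| Allocation disclosed | After the baseline assessment at the home visit | Same section |
| Actiheart worn | Three days from fitting | Same section |
| Device collected, IPAQ completed | After the wear period | Same section |
| IPAQ in women without a device | Not stated | – |

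In the disclosure sentence, the words about the home visit can attach in two ways.

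1. To the act of informing: women are told at the visit, before any activity data exist.
2. To the baseline assessment: the trigger is completion of the part done at the visit. By the section's own exception, that part excludes the wear period and the IPAQ.

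Neither attachment makes disclosure wait for the device. The sentence also sits badly with the statement that baseline covers every outcome measure, because physical activity is one of them and is not finished at the visit.

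**Effect on the estimate**

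No figure in the document bears on this point. The sample-size figures concern EPDS and do not change.

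The analysis of covariance estimates

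estimate = D6 − b × d0

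where D6 is the true six-month arm difference in activity, b is the within-arm slope of follow-up on baseline, and d0 is the arm difference that knowledge of allocation has put into the baseline value. With a true pre-randomisation baseline, d0 is zero in expectation. Otherwise the bias is −b × d0.

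The inputs below are assumptions: d0 of 0.1 to 0.3 SD and b of 0.4 to 0.6.

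- Smallest: 0.4 × 0.1 = 0.04 SD
- Largest: 0.6 × 0.3 = 0.18 SD
- If disclosure waited: d0 = 0, so the bias is 0

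The same result can be put in relative terms without assuming an effect size. If a share f of the six-month effect is already in the baseline value, so that d0 = f × D6, the analysis keeps 1 − b × f of the true effect. These values are also assumed:

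| f | b | Kept by formula | Kept in simulation |
|---|---|---|---|
| 0.10 | 0.3 | 1 − 0.03 = 97% | 96.8% |
| 0.25 | 0.5 | 1 − 0.125 = 87.5% | 88.3% |
| 0.50 | 0.7 | 1 − 0.35 = 65% | 65.6% |

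The simulation used 400,000 women per row and agrees with the formula to within about one percentage point.

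**Direction.** More activity in the exercise arm during the wear days pulls the estimated effect down. A shift the other way would inflate it.

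**The case against.** The strongest reply is that baseline is said to include every outcome measure, so completing it must include the device and the IPAQ, and disclosure would follow both. Site practice may well have been so, and then there is no bias. But that reading has to treat as done at the home visit measurements that the same section places days later. The Case definition sentence does not settle it either, since the IPAQ is the exception to completion at the visit. What stands is that disclosure at the visit is the natural reading of the wording and not an established fact.

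Other points also stand.

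- The late sequence is described only for device wearers. A reader might infer that every woman's baseline IPAQ follows disclosure, but the article is silent on the other half.
- The exercise consultations fall in months 1 and 2, and the pedometer comes with the first. Nothing places that contact within the wear days, so a shift would have to come mainly from knowing the arm.
- It is tempting to express the bias as a percentage of 0.5 SD. That figure is the target difference for EPDS, and the document gives none for activity.
- Covariate detail for each secondary outcome may sit in an analysis plan not shown. The article's own text nonetheless extends the baseline-adjusted method to these outcomes without a safeguard.

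The exercise diaries do not replace the comparison, because only the intervention group completes them.

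**Conclusion.** The point holds as a defect in the stated sequence, limited to the physical activity outcomes. As written, nothing keeps allocation concealed from the woman until her baseline accelerometer record, and at least in device wearers her IPAQ, has been obtained. The planned adjustment would then use a value open to influence from allocation.

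The size cannot be found from the documents. It is 0.04 to 0.18 SD under the assumed shift and slope, and zero if disclosure waited.

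A reader might infer that the trial's main result is compromised. It is not: the EPDS baseline is the home-visit score. This is a correction to the handling of secondary outcomes, cheap to make and worth making, and not a threat to the primary conclusion.

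**What to change.** - State that allocation is generated and disclosed only after the Actiheart has been collected and the IPAQ completed. The team already makes this contact.
- State that women without a device complete the IPAQ at the home visit, before randomisation.
- For any woman whose activity was measured after disclosure, do not use that value as a baseline covariate in any model of the activity outcomes.

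**Cost.** Device wearers learn their allocation a few days later, with no extra visit. If the covariate is dropped, some precision is lost on the activity outcomes. With equal variances at the two times, the slope equals the correlation, and the standard error without adjustment is larger by 1/√(1 − b²). That is 1/√0.84 = 1.09 at b = 0.4 and 1/√0.64 = 1.25 at b = 0.6, again with assumed slopes. The sample size of 208 is unaffected.

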#### Process outcomes/adherence

Participants randomised to the exercise intervention group are asked to complete exercise diary logs that detail the dose/amount and type of exercise completed during weeks 4, 8, 12, 16, 20 of the intervention. Logs are completed with the PAF either in person or over the phone or sent and returned by post.

### Sample size

A sample of 83 patients randomised to each group will be sufficient to detect a 1.95 unit difference (effect size = 0.5 standard deviations) in EPDS score between the groups at the 6 month follow-up with 90% power, 5% significance level. The numbers required increase to 104 in each arm when allowance is made for a 20% dropout rate at 6 month follow-up (n = 208). A sample size of 208 would also be sufficient to detect a 1.76 unit difference (effect size 0.45) in EPDS score between the groups at 6 month follow-up with 80% power, 5% significance level. We would expect maximum impact at the end of the intervention and exercise participation to tail off over time; therefore six months has been selected as the primary follow-up point.

### Analysis plan

Baseline characteristics of participants will be tabulated by randomisation arm. Primary analysis will compare mean EPDS score at the 6 months follow-up between trial groups, adjusting for baseline scores using analysis of covariance. Similar analyses will be conducted for the secondary outcomes. Secondary analyses will adjust for covariates (e.g. age, gender, initial weight, ethnicity, education level) again using analysis of covariance. To explore any longer term effects, a repeated measures mixed model analysis of the primary and secondary outcomes will be undertaken, comparing groups across the 6 and 12 month time points. EPDS score taken at the home visit will be used as the baseline score in analyses. We will also report data on the proportion of women in each group who score less than 13 points on the EPDS at follow-up. All analysis will be by intention to treat.

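### The ANCOVA for the non-EPDS secondary outcomes does not name the EPDS severity used to stratify randomisation; adding it would remove a small conservatism at almost no cost

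*Protocol article*

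**What the plan says.** Under Assessment of outcomes and blinding, the protocol article names a single stratification factor: "The randomisation is stratified by baseline EPDS score (13–16 or ≥16").

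The Analysis plan section then describes four layers of analysis:

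- **Primary outcome.** Six-month EPDS is compared between groups, "adjusting for baseline scores using analysis of covariance".
- **Secondary outcomes.** "Similar analyses will be conducted for the secondary outcomes".
- **Covariate-adjusted analyses.** "Secondary analyses will adjust for covariates (e.g. age, gender, initial weight, ethnicity, education level) again using analysis of covariance".
- **Longer-term analysis.** "a repeated measures mixed model analysis of the primary and secondary outcomes will be undertaken, comparing groups across the 6 and 12 month time points". No covariates are given for this model.

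The same section adds that the "EPDS score taken at the home visit will be used as the baseline score in analyses".

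The secondary outcomes listed in the article are SF-12, EQ-5D, body image, vitality, social support, exercise self-efficacy, physical activity, and body weight and height.

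**The concern.** Balancing the arms on a prognostic factor by design reduces the true sampling variation of the treatment difference. A model that leaves the factor out still counts its contribution as residual noise. The reported standard error is then larger than the true one, intervals are a little too wide, and tests reject less often than their nominal level.

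For six-month EPDS this hardly matters, because continuous baseline EPDS is in the model and carries the band. For the other outcomes, an analysis similar to the primary one most naturally means ANCOVA on that outcome's own baseline. Neither EPDS nor its band then enters, although depression severity could plausibly predict later vitality or mental quality of life even after their own baselines are allowed for. What is at stake is some unnecessary width in the secondary-outcome intervals. Validity is not in question.

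**Working it through.** **1. The plan's own figure.** The Sample size section says 83 per arm is "sufficient to detect a 1.95 unit difference (effect size = 0.5 standard deviations") "with 90% power, 5% significance level". The implied SD is 1.95 / 0.5 = 3.9. With a two-sided test (sidedness is not stated), n per arm = 2 × ((1.960 + 1.282) / 0.5)² = 84.1, or 85 with the t correction. At 83 per arm the power is 89.6%, and 83 / 0.8 = 104 after dropout. The stated size therefore reproduces closely. It concerns EPDS only; no secondary outcome has a power target.

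**2. Formula.** Let r be the partial correlation between stratum and outcome, given the covariates already in the model. With arms balanced within strata,

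f = SE reported without the stratum / SE reported with it = 1 / √(1 − r²).

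This gives f = 1.005 at r = 0.1, 1.021 at r = 0.2 and 1.048 at r = 0.3. For two equal strata whose means differ by d residual SDs, the same ratio is f = √(1 + d²/4).

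The true type I error of the test without the stratum is about 2Φ(−1.96f). If the test with the stratum has power Φ(θ − 1.96), the test without it has about Φ(θ − 1.96f). Taking θ = 2.80 sets the first of these at 80%, purely as an illustration.

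**3. Assumed inputs.** The documents give no correlation between EPDS band and any secondary outcome, so a range is shown. The first three rows assume correlations between EPDS and the outcome's baseline, between baseline and outcome, and between EPDS and outcome, with a median split on EPDS. The split has correlation √(2/π) = 0.798 with EPDS. In the third row, for example, r = (0.359 − 0.399 × 0.5) / √((1 − 0.159)(1 − 0.25)) = 0.201.

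| Assumption (own baseline in model) | f | True type I error without stratum | Power lost from 80% |
|---|---|---|---|
| Correlations 0.2, 0.6, 0.15 (r = 0.030) | 1.0005 | 5.0% | under 0.1 point |
| Correlations 0.4, 0.5, 0.3 (r = 0.097) | 1.005 | 4.9% | 0.3 points |
| Correlations 0.5, 0.5, 0.45 (r = 0.201) | 1.021 | 4.5% | 1.2 points |
| Residual effect d = 0.3 SD: √(1 + 0.0225) | 1.011 | 4.7% | 0.6 points |
| Residual effect d = 0.8 SD: √(1 + 0.16) | 1.077 | 3.5% | 4.5 points |

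**4. Simulation check of the first three rows.** There were 166 analysed, permuted blocks of 4 within stratum (block size assumed) and 4,000 replicates. Adding the stratum to a model that already held the outcome's own baseline changed the mean reported SE as follows:

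- 0.1244 to 0.1243 (0.1%)
- 0.1345 to 0.1339 (0.4%)
- 0.1345 to 0.1317 (2.1%)

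These match the closed form. Type I error without the stratum was 4.75%, 5.30% and 4.85%. With a simulation error of √(0.05 × 0.95 / 4000) = 0.34 points, none of these can be told apart from 5%.

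**5. Continuous EPDS instead of the band.** In the third scenario, adding continuous EPDS lowered the SE from 0.1345 to 0.1298 (3.5%), against 2.1% for the band.

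**6. Model already holding continuous EPDS.** Adding the stratum gained nothing: 0.1478 without it, 0.1481 with it. This is why the primary analysis is essentially unaffected.

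**7. No baseline covariate at all.** If a repeated-measures model truly had none, adding the stratum would lower the SE by 0.7% to 6.7% (0.1551 to 0.1540, and 0.1549 to 0.1445). These are single-time-point simulations; no mixed model was simulated.

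**The case against.** The strongest reply is that the article is silent rather than wrong. It condenses the analysis into one paragraph, the covariate list is open-ended, and the full analysis plan may name the stratum. This stands in part. A reader might infer that the secondary and repeated-measures models exclude the stratum, but no sentence says so, and the repeated-measures covariates are simply not given. What remains is that the article does state a form for the secondary ANCOVA, and its natural reading does not bring EPDS in. The sentence fixing the home-visit EPDS as the baseline score could be stretched to put EPDS in every model. It more naturally says which EPDS reading counts as baseline. For EPDS itself, it suggests that the repeated-measures model would also hold continuous baseline EPDS, so little would be lost there.

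Three stronger readings are tempting and are not supported:

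- **That the primary analysis is mis-specified.** It adjusts for baseline EPDS, and adding the band gains nothing.
- **That precision is lost or validity threatened.** Stratified allocation has already balanced the arms. With no covariates and correlations 0.4, 0.5 and 0.3, the simulated spread of the estimate was 0.1503 with or without the stratum. Only the reported SE differed (0.1549 against 0.1503). Estimates stay unbiased and type I error is not inflated.
- **That the band comes from a different EPDS reading than the analysis baseline.** The lower limit of 13 echoes the telephone screening threshold of more than 12. But the article stratifies on the baseline score and takes that score at the home visit, before randomisation, so the plain reading is one and the same score.

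The size is also open to challenge. The 8% figure needs a residual severity effect of 0.8 SD after own-baseline adjustment. That is larger than the 0.5 SD treatment effect the trial is powered for, and hard to credit for weight or measured activity. This objection stands, and it is why the severity is low.

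**Conclusion.** The point holds in a limited form. The trial's only stratification factor is not named in the stated analysis of the non-EPDS secondary outcomes. If those outcomes are adjusted for their own baseline alone, the reported standard errors are too large by about 0.1% to 2% under modest assumed correlations, and by about 8% if the residual severity effect is 0.8 SD. The corresponding type I error runs from essentially 5% down to about 3.5%.

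These figures rest on assumed associations, roughly equal strata and 83 analysed per arm; the documents supply only the last. The direction is always conservative, and no conclusion about six-month EPDS depends on it. This is a free improvement of low severity, not an error that undermines the trial.

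**What to change.** Add one sentence to the Analysis plan: every ANCOVA of a non-EPDS secondary outcome, and the repeated-measures models, will include baseline EPDS (continuous) or the randomisation stratum as a fixed covariate, alongside the outcome's own baseline. Continuous EPDS did slightly better in the check above. It also avoids a coding problem, because the printed bands overlap at a score of 16. If the stratum is used, take it as recorded by the randomisation service. The primary EPDS ANCOVA needs no change on this account.

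The cost is one or two degrees of freedom out of about 166 analysed. The data are already collected, and fixing the covariate in advance leaves no later choice to defend.

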### Intervention

#### Rationale

In developing the exercise intervention consideration was given to the Cochrane review [35] of physical activity interventions which reported a greater consistency of effect estimates for those studies where there were four or more contacts between those delivering the intervention and participants, compared to studies where there were less than four contacts. This review also showed that a mixture of professional guidance and self-direction plus on-going support leads to more consistent effect estimates. The intervention will use the processes of change from the Transtheoretical Model conceptual framework [36] as vehicles to promote and facilitate exercise behaviour change.

Different types of exercise interventions have been used in previous trials involving depressed postnatal women as well as other depressed populations, including centre/supervised classes, community based group pram walks and home based exercise. Whilst all have been shown merit, home based exercise interventions are attractive because they are low cost. For women with PND, complications such as childcare responsibilities, fatigue and breastfeeding routines may reduce their opportunities and enthusiasm for exercise [37], particularly if they involve significant travel time or are offered at specific times of the day. Thus, any programme that promotes exercise in this population will need to take account of such factors. It is for these reasons that we have chosen to offer women a home/community based exercise intervention, which has potential to be implemented in different primary care contexts, if shown to be effective. A home-based programme involving consultations and phone calls was also found to be feasible in our pilot trial [19], where the exercise group reported more moderate intensity exercise and significantly higher self-efficacy for exercise than usual care.

Six months has been selected as the intervention duration as this is likely to be the maximum time period for which a pragmatic, low cost intervention can be viable.

